### Figure GZEA.1. Dose escalation for Protocol J1T-MC-GZEA.

This is a randomized double-blinded SAD design in dyslipidemic but otherwise healthy male and female subjects, investigating the safety, tolerability, PD, and PK of LY3475766 versus placebo.

Subjects will be enrolled in 6 cohorts:

- Cohort 1: 10 mg LY3475766 or placebo IV
- Cohort 2: 30 mg LY3475766 or placebo IV
- Cohort 3: 100 mg LY3475766 or placebo SC
- Cohort 4: 300 mg LY3475766 or placebo SC
- Cohort 5: 600 mg LY3475766 or placebo SC
- Cohort 6: 1000 mg LY3475766 or placebo IV

Doses and the number of cohorts may be adjusted based on ongoing review of the PK, safety, and tolerability data.

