### **9.3.2 Pharmacokinetic Statistical Methodology**

PK dose proportionality will be assessed using a power model. Log-transformed  $C_{\max}$ ,  $\text{AUC}(0-t_{\text{last}})$  and  $\text{AUC}(0-\infty)$  estimates will be evaluated using a power model (where log-dose acts as an explanatory variable) to estimate ratios of dose-normalized geometric means and corresponding 90% confidence intervals (CIs).

The estimated ratio of dose-normalized geometric means of PK parameters between the highest and lowest doses will be used to assess dose proportionality. Between subject variability estimates will also be provided.

Example SAS code for the analysis:

```
proc mixed data=xxx;  
model log_pk = log_dose / alpha=0.1 cl solution outpred=resids ddfm=kr;  
estimate 'xx mg' intercept 1 log_dose yy / alpha=0.1 cl; /*Log value of xx*/  
estimate 'zz mg - xx mg' log_dose pp / alpha=0.1 cl; /*Difference in log  
values of zz and xx*/  
ods output solutionf=est;  
ods output estimates=estims;  
run;
```

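### SAP 9.3.2: the example dose-proportionality code omits the dose-normalization step that its text requires, so its contrast estimates the log of the raw ratio

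*Combined protocol and SAP*

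**What the plan says.** The text of SAP 9.3.2 names the target twice. It fits a power model to log-transformed Cmax, AUC(0-tlast) and AUC(0-∞) in order to estimate dose-normalized ratios with 90% CIs, and it then says: "The estimated ratio of dose-normalized geometric means of PK parameters between the highest and lowest doses will be used to assess dose proportionality".

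The example code below that text has these parts:

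- The model is "model log_pk = log_dose / alpha=0.1 cl solution outpred=resids ddfm=kr". Neither the code nor the text says that `log_pk` is divided by dose.
- The comparison of two doses is "estimate 'zz mg - xx mg' log_dose pp / alpha=0.1 cl". The comment beside it defines pp as the difference between the log "values of zz and xx".
- The estimates are then written to a dataset with "ods output estimates=estims". No exponentiation and no adjustment for the dose ratio is shown or described.

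The extreme doses come from the SAP's cohort list: "Cohort 1: 10 mg LY3475766 or placebo IV" and "Cohort 6: 1000 mg LY3475766 or placebo IV".

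Protocol 10.3.2.2 describes the same analysis more briefly. It says only that the power parameter, that is the slope, will be evaluated. Neither document gives an acceptance limit or a reference value.

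**The concern.** The text and the code describe different quantities. Under proportional PK a dose-normalized ratio equals 1, while a raw ratio equals the ratio of the doses. The SAP bases its assessment on the first, and its only written computation leads to the second.

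PK characterization is a secondary objective, with AUC and Cmax among its endpoints. Two things are at stake. A raw ratio might be reported under a dose-normalized label. Or a correction might be settled only once the data are in hand, because the SAP states neither the step nor the null value against which a slip would show.

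**Working it through.** The documents give no numerical result for this analysis, so there is no stated figure to reproduce. The check is algebra, followed by the planned doses.

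**Inputs**

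- Lowest and highest dose: 10 mg and 1000 mg, both IV (SAP section 5).
- pp = ln(1000/10) = ln(100) = 4.605.
- Predicted human AUC: 1324.9 µg·h/mL at 10 mg and 132485.9 µg·h/mL at 1000 mg (Protocol Table GZEA.2).

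**Algebra.** The model is ln(PK) = a + b·ln(dose).

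- Coded contrast: b·ln(zz/xx). Exponentiated, it is (zz/xx)^b, the raw ratio of geometric means.
- Dose-normalized ratio: (zz/xx)^b ÷ (zz/xx) = (zz/xx)^(b − 1), with log (b − 1)·ln(zz/xx).
- Difference on the log scale: ln(zz/xx), a known constant. The estimate and both confidence limits shift by the same amount, so the width on the log scale does not change.

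**Values for 1000 versus 10 mg**

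| Slope b | Coded contrast (log scale) | Exponentiated | Dose-normalized ratio |
|---|---|---|---|
| 0.8 | 3.684 | 39.8 | 0.398 |
| 0.9 | 4.145 | 63.1 | 0.631 |
| 1.0 | 4.605 | 100 | 1.000 |
| 1.1 | 5.066 | 158.5 | 1.585 |
| 1.2 | 5.526 | 251.2 | 2.512 |

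**Check with the protocol's own predictions.** 132485.9 ÷ 1324.9 = 99.997, so the slope is 1.0000. The coded contrast back-transforms to 99.997, and the dose-normalized ratio is 99.997 ÷ 100 = 0.99997.

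**Effect on the interval (illustration).** Assume b = 1, a between-subject log SD of 0.3, six subjects at each of the six doses and no route effect.

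- The sum of squares of log dose about its mean is 6 × 15.997 = 95.98.
- The standard error of the contrast is 4.605 × 0.3/√95.98 = 0.141.
- With t(34) = 1.691 the half-width is 0.238.
- Centred on the true value, the exponentiated contrast is 100 (90% CI 79 to 127). The dose-normalized ratio is 1.00 (0.79 to 1.27).

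In 20,000 simulated proportional data sets with an assumed CV of 30%, for the IV doses alone and again for all six doses, the exponentiated interval never contained 1. After division by 100 it contained 1 in about 90% of runs, as it should. Fitting ln(PK/dose) with the same contrast gave the same estimate and limits as dividing by 100.

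The algebra does not depend on how route is handled. Both extreme doses are IV, and the factor is the same within the IV cohorts alone.

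**The case against.** The strongest reply is that the text is the plan and the code only an example, full of placeholders. Other snippets in this SAP are also incomplete. The treatment-comparison models in 9.4.1 and 9.5.4 list only treatment as a class variable, and the log transformation for TG and LDL-C in 9.4.1 appears only in the text. Some post-processing is needed anyway, because the text promises ratios and the code exports log-scale estimates. Dividing by a known dose ratio at that point would be exact and need no refit. The table, figure and listing shells, which are not available here, might specify it.

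Most of this stands. A reader might infer that the code itself reports 100 for proportional PK. It does not: at slope 1 its literal output is 4.605 on the log scale, and 100 appears only after an exponentiation that is also not shown. A reader might also infer that proportional PK will be declared non-proportional. The documents do not support that. The same code requests the slope with its 90% CI, a mislabelled ratio of 100 would visibly contradict a slope of 1, and there is no acceptance limit that would flip a decision.

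The mismatch itself remains. In 9.4.1 the SAP does describe its back-transformation in words; in 9.3.2 it does not. Nor can `log_pk` readily be read as already dose-normalized. The text describes it as the log-transformed PK parameters, and the first ESTIMATE line, labelled with a single dose, gives a predicted log geometric mean at that dose. SAP section 3 makes the SAP and shells the template for the study report and says the SAP supersedes the protocol's statistical considerations. So the protocol's reliance on the slope limits the harm but does not supply the missing step.

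**Conclusion.** The point holds as a mismatch between text and example code. Followed as written and then exponentiated, the contrast gives the raw ratio, and the estimate and both 90% limits are too large by exactly the dose ratio. That is 100 for the planned 10 and 1000 mg doses, or the actual ratio if the doses are adjusted. The factor needs no assumption about variability or sample size; only the illustrative interval does.

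The practical weight is small. The slope and its CI are correct, no primary endpoint or sample size is involved, and a value near 100 would probably be noticed. The documents do not show that the final report would contain the error, only that the step preventing it is not written down.

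**What to change.** In SAP 9.3.2, choose one of the following:

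- Keep `log_pk` as the response, and state that ln(zz/xx) is subtracted from the estimate and from both 90% limits before exponentiation.
- Model log(PK/dose) on log dose and leave the dose-comparison ESTIMATE line as it is. The fitted slope is then b − 1, so its reference becomes 0 and 1 must be added to recover the protocol's power parameter. The single-dose ESTIMATE line becomes a dose-normalized mean.

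The first option leaves the slope output as it stands. With either, state that the reference value for the dose-normalized ratio is 1. The cost is one line of code or text, with no new data and no change to the design.

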## 9.4 Pharmacodynamic Assessment

### 9.4.1 Pharmacodynamic Analysis

The following PD parameters will be listed and summarized by treatment and timepoint (as appropriate):

- Fasting lipid panel (TG, total cholesterol, low-density lipoprotein cholesterol [LDL-C] (direct assay from central lab), very low-density lipoprotein cholesterol [calculated], high-density lipoprotein cholesterol, non-high-density lipoprotein cholesterol [calculated], apolipoproteins [apoA-I, apoB, and apoC-III]), change from baseline (Day 1 predose) and percentage change from baseline.
- Fasting angiotensin-like protein 3/8 complex levels, change from baseline (Day 1 predose) and percentage change from baseline.

For the fasting lipid panel (except for apoB and angiotensin-like protein 3/8 complex levels), summary statistics will include arithmetic mean, standard deviation, geometric mean, CV%, median, minimum, maximum, Q1, Q3 (due to the distribution of the data). For apoB and angiotensin-like protein 3/8 complex levels, standard summary statistics will be presented.

In addition, a mixed-model repeated-measure model will be used to evaluate treatment effect for the parameters change from baseline LDL-C, TG, apoB and angiotensin-like protein 3/8. The model will include treatment, timepoint, and treatment by time point interaction as fixed effects, subject as a random effect and baseline as a covariate. An unstructured covariance structure will be used and a compound symmetric structure can be used if the model fails to converge.

Example of SAS code (for the change from baseline analysis) as follows.

```
proc mixed data=xxx;  
class treatment;  
model change = baseline treatment timepoint treatment*timepoint  
/residual ddfm=kr;  
repeated timepoint / subject=subject type=UN;  
lsmeans treatment*timepoint / cl pdiff alpha=0.1;  
ods output lsmeans=lsm diffs=estims;  
run;
```

For the above analysis, TG and LDL-C will be log transformed prior to analysis, and back-transformed to calculate percent changes from baseline.

Absolute and change from baseline arithmetic mean time profiles of the PD parameters will be produced.

## **9.5 Safety and Tolerability Assessments**

### **9.5.1 Adverse events**

Where changes in severity are recorded in the Case Report Form (CRF), each separate severity of the adverse event (AE) will be reported in the listings, only the most severe will be used in the summary tables. A pre-existing condition is defined as an AE that starts before the subject has provided written informed consent and is ongoing at consent. A non-treatment emergent AE is defined as an AE which starts after informed consent but prior to dosing. A treatment-emergent AE is defined as an AE which occurs postdose or which is present prior to dosing and becomes more severe postdose.

All AEs will be listed. Treatment-emergent AEs will be summarized by treatment, severity and relationship to the study drug. The frequency (the number of AEs, the number of subjects experiencing an AE and the percentage of subjects experiencing an AE) of treatment-emergent AEs will be summarized by treatment, Medical Dictionary for Regulatory Activities (MedDRA) version 22.0 system organ class and preferred term. The summary and frequency AE tables will be presented for all causalities and those considered related to the study drug. Any serious AEs will be listed.

Discontinuations due to AEs will be listed.

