| Single-lead telemetry     |                   | X  | X                | X | X | X | X | X | X | X |        |        |        |        |        |           |    | Day 5 through 8 are SC only. Telemetry is continuous from 12 h predose to 72 h postdose (IV cohorts) or 168 h postdose (SC cohorts). |
| Seated PR                 | X                 | X  | X                | X | X | X | X | X | X | X | X      | X      | X      | X      | X      | X         | X  | Day 1: Within 1 h before dosing and 5 to 15 min, 1 h (+ 30 min), and 8 h after starting dosing; Days 5-7 for SC cohorts only         |
| Body temperature          | X                 | X  | P                | X | X | X |   |   |   | X | X      | X      | X      |        |        | X         | X  | Any time before breakfast                                                                                                            |
| Seated BP                 | X                 | X  | X                |   |   |   |   |   |   |   |        | X      |        | X      |        | X         | X  | Day 1: 5 to 15 min and 1 h (+ 30 min) after starting dosing                                                                          |
| AOBPM                     |                   |    | P, 6 h           | X | X | X | X | X | X | X | X      |        | X      |        | X      |           |    | Days 5 through 7 are SC only. See Section 9.4.2. for more details.                                                                   |
| Adverse event reporting   | X                 | X  | ←-----→          |   |   |   |   |   |   |   |        |        |        |        |        | X         |    |                                                                                                                                      |

| Procedure               | Screening         |    | Treatment Period |   |   |   |   |   |   |        |        |        |        |        |        | Follow-up | ET | Notes |
|-------------------------|-------------------|----|------------------|---|---|---|---|---|---|--------|--------|--------|--------|--------|--------|-----------|----|-------|
|                         |                   |    | Week 1           |   |   |   |   |   |   | Week 2 | Week 3 | Week 4 | Week 5 | Week 7 | Week 9 | Week 13   |    |       |
| Day                     | Day -28 to Day -2 | -1 | 1                | 2 | 3 | 4 | 5 | 6 | 7 | 8      | 15 ±2  | 22 ±2  | 29 ±2  | 43 ±5  | 57 ±5  | 85 ±5     |    |       |

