**Figure GZEA.1. Dose escalation for Protocol J1T-MC-GZEA.**

Potential subjects will be screened to assess their eligibility to enter the study within 28 days prior to Day 1. In case of safety concerns, participants may be required to stay at the clinical site for a longer period at the discretion of the investigator. Subjects in all cohorts will return to the clinical research unit (CRU) as outpatients at predetermined visits for up to approximately 84 days postdose for follow-up assessments. In case a subject cannot come to the site for 1 or several outpatient visits, home visits may potentially be performed instead, depending on the circumstances and if agreed upon between investigator and sponsor.

Subjects will be confined at the CRU:

- from Day -1 (the day before dosing) to Day 4 (72 hours postdose) for IV cohorts (with outpatient visits starting on Day 8), and
- from Day -1 (the day before dosing) to Day 8 (168 hours postdose) for SC cohorts.

This is a randomized double-blinded SAD study in dyslipidemic but otherwise healthy male and female subjects investigating the safety, tolerability, PD, and PK of LY3475766 versus placebo.

Subjects will be enrolled in 6 cohorts:

- Cohort 1: 10 mg LY3475766 or placebo IV
- Cohort 2: 30 mg LY3475766 or placebo IV
- Cohort 3: 100 mg LY3475766 or placebo SC
- Cohort 4: 300 mg LY3475766 or placebo SC
- Cohort 5: 600 mg LY3475766 or placebo SC
- Cohort 6: 1000 mg LY3475766 or placebo IV

Safety and tolerability will be assessed throughout the study by means of vital sign measurements, safety laboratory tests, ECGs, physical examinations, automated office blood pressure monitoring (AOBPM), and AE recording. Sampling schedules, doses, and number of cohorts may be adjusted based on ongoing review of the PK, safety, and tolerability data. Additional follow-up visits may occur depending upon the PK and/or safety data.

Doses and the number of cohorts may be adjusted based on ongoing review of the PK, safety, and tolerability data at visits described in Section 2.

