## 5.2. Number of Participants

Up to 70 subjects may be enrolled so that 48 subjects (LY3475766: 36, Placebo: 12) have sufficient evaluable data.

For purposes of this study, a subject completes the study when all scheduled procedures shown in the Schedule of Activities have been completed.

Subjects who are randomized and who are discontinued from the study (providing that discontinuation did not result from a safety finding) may be replaced to ensure that enough subjects complete the study.

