## **7.2. Method of Treatment Assignment**

Subjects who meet all criteria for enrollment will be randomized to 1 of the study treatment groups on Day 1. Subjects will be randomized in a 3:1 ratio to receive LY3475766 or placebo.

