#### **9.4.3. Telemetry**

For each subject, single-lead ECG telemetry will be performed during each stay at the CRU involving at least 1 night (see Schedule of Activities in Section 2). The telemetry system has standard alarms to alert the clinical staff to any detected abnormalities, for example, cardiac arrhythmias, prolongation of QT, during which additional 12-lead ECGs may be obtained at the investigator's discretion. These may also be performed in the event of technical or logistical impediments to the use of telemetry. In order to bathe, subjects may remove the telemetry device for up to 1 hour, which should be documented.

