## 6. TREATMENTS

The following is a list of the study treatment names that will be used in the TFLs.

| Study Treatment Name | Treatment order in TFL |
|----------------------|------------------------|
| Placebo              | 1                      |
| 10 mg LY3475766 IV   | 2                      |
| 30 mg LY3475766 IV   | 3                      |
| 100 mg LY3475766 SC  | 4                      |
| 300 mg LY3475766 SC  | 5                      |
| 600 mg LY3475766 SC  | 6                      |
| 1000 mg LY3475766 IV | 7                      |

Placebo data will be pooled. The above dose levels will be updated on the TFLs for the actual dose received.

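### Telemetry runs 72 h in IV cohorts and 168 h in SC cohorts, but adverse-event percentages sit beside one placebo column pooled over routes, so monitoring-detected heart-rate and rhythm events tend to look too frequent in SC arms and too rare in IV arms

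*Combined protocol and SAP*

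**What the plan says.** - **Monitoring.** The telemetry row of the protocol's Schedule of Activities (Section 2) states: "Telemetry is continuous from 12 h predose to 72 h postdose (IV cohorts) or 168 h postdose (SC cohorts". This follows confinement in protocol 5.1, where IV subjects stay "from Day -1 (the day before dosing) to Day 4 (72 hours postdose) for IV cohorts"; SC subjects stay four days longer, until 168 h. On Days 5 to 7 the schedule gives pulse rate, automated office blood pressure (AOBPM) and directed examinations to SC cohorts only.
- **Role of telemetry.** Protocol 9.4.3: "The telemetry system has standard alarms to alert the clinical staff to any detected abnormalities". Any extra 12-lead ECG is then at the investigator's discretion.
- **Adverse-event table.** SAP 9.5.1 counts any postdose event as treatment-emergent and tabulates by treatment: "The frequency (the number of AEs, the number of subjects experiencing an AE and the percentage of subjects experiencing an AE". It gives no route split and no adjustment for time monitored.
- **Placebo.** SAP 6: "Placebo data will be pooled".
- **Numbers.** Protocol 5.2: "Up to 70 subjects may be enrolled so that 48 subjects (LY3475766: 36, Placebo: 12) have sufficient evaluable data". Protocol 7.2: "Subjects will be randomized in a 3:1 ratio to receive LY3475766 or placebo".
- **ECGs.** Under SAP 9.5.5 ECG data are not presented, and clinically significant findings appear only as adverse events.

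**The concern.** A slow heart rate or arrhythmia without symptoms is more likely to be noticed while an alarmed monitor is running. SC subjects have 7 postdose days of it and IV subjects 3. Pooled placebo mixes the two and matches neither set of active arms. The numerator of the percentage depends partly on monitoring time, and the denominator ignores it.

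Route is also tied to dose: 10, 30 and 1000 mg are IV; 100, 300 and 600 mg are SC. A difference in ascertainment can therefore appear as a dose pattern, flattering the top dose and penalising the middle ones. Adverse-event incidence is a primary endpoint (protocol Section 4), and a fall in heart rate is the one risk anticipated in protocol 3.3. Because ECG data are not tabulated, the adverse-event tables are the main place where a rhythm finding is summarised.

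**Working it through.** **Planned numbers.** 48 × 3/4 = 36 active and 48 × 1/4 = 12 placebo, as stated. Over 6 cohorts, 48/6 = 8 each, or 6 active and 2 placebo. With three IV cohorts (1, 2, 6) and three SC cohorts (3, 4, 5) this gives 6 IV and 6 SC placebo subjects. The documents do not state the split by route, so it is an assumption. The amendment summary says that Cohort 4 (SC) must be repeated, which could make it 6 IV and 8 SC.

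**Limiting case: rare events, constant background rate, found by telemetry only.** Detection is proportional to hours monitored.
- Pooled placebo: (6 × 72 + 6 × 168)/12 = 120 h. SC ratio 168/120 = 1.40; IV ratio 72/120 = 0.60.
- Placebo 6 IV and 8 SC: (6 × 72 + 8 × 168)/14 = 126.9 h. SC 168/126.9 = 1.32; IV 72/126.9 = 0.57.

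**Events not rare.** The proportion with at least one event is P = 1 − exp(−λ × days), with 3 days (IV) and 7 days (SC). The documents give no background rate, so λ is assumed. Placebo is split 6/6, and the shift is 6 × the difference from placebo.

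| λ per day | IV | SC | Pooled placebo | SC ratio | IV ratio | Shift, subjects per arm of 6 |
|---|---|---|---|---|---|---|
| 0.01 | 3.0% | 6.8% | 4.9% | 1.39 | 0.61 | 0.11 |
| 0.05 | 13.9% | 29.5% | 21.7% | 1.36 | 0.64 | 0.47 |
| 0.10 | 25.9% | 50.3% | 38.1% | 1.32 | 0.68 | 0.73 |

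With placebo 6/8 and λ = 0.05, pooled placebo is (6 × 13.9 + 8 × 29.5)/14 = 22.8%. The ratios are 1.29 and 0.61, and the shifts are 0.40 (SC) and 0.53 (IV) subjects per arm of 6.

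**Detection by other means (placebo 6/6, rare events).**
- If half of the events in the placebo column are found equally in both routes by other means: 1 ± 0.4 × 0.5, or 1.20 and 0.80.
- If detection off telemetry has sensitivity f relative to telemetry over the rest of 84 days (2016 h), effective hours are 72 + f × 1944 (IV) and 168 + f × 1848 (SC).
  - f = 0.05: 169.2 and 260.4, mean 214.8; ratios 1.21 (SC) and 0.79 (IV).
  - f = 0.10: 266.4 and 352.8, mean 309.6; ratios 1.14 and 0.86.
  - f = 1: both ratios are 1.00.

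**After the fix.** If only onsets in the common 72 h are counted, every subject contributes 72 h and both ratios are 1.00, with all placebo subjects kept.

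**The case against.** The strongest reply is that telemetry is only one route into the adverse-event table. Adverse events are collected to Day 85 in every cohort. Pulse rate is taken in both routes on Days 1 to 4 and at every visit from Day 8, and 12-lead ECGs on Days 1, 2, 8, 29 and 85. This stands. A reader might infer that all heart-rate and rhythm events are distorted by 1.40 and 0.60. The documents do not support that: these are the telemetry-only limit, and detection by other means pulls the ratios towards 1.

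Second, an alarm is not an adverse event. Protocol 9.4.4 asks for ECG findings to be reported when they are clinically significant and lead to a diagnosis. Subjects are screened for low heart rate, abnormal ECGs and rate-lowering drugs, and a finding already seen before dosing counts only if it worsens. A background of 0.05 per day, about 30% of SC subjects in a week, is therefore probably high. This also stands and keeps the absolute shift small.

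Third, the table is descriptive, the treatment labels show the route, and all events are listed. A reader might infer that the anticipated heart-rate risk rests on this table alone. It does not: SAP 9.5.4 compares AOBPM pulse rate for each dose with placebo at each timepoint, with 90% intervals, and relates heart rate to concentration. Those analyses use scheduled readings, however, and do not cover events found between them.

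None of this equalises ascertainment in SAP 9.5.1. Intermittent checks are unlikely to match continuous alarmed monitoring for transient, symptomless events.

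**Conclusion.** The point holds as an ascertainment bias of known direction and modest absolute size. With no drug effect, monitoring-detected heart-rate and rhythm events are expected to be over-represented in SC arms and under-represented in IV arms relative to pooled placebo. With a 6/6 placebo split, the ratios run from 1.40 and 0.60 (telemetry only) through 1.20 and 0.80 (half found otherwise) to 1.14 and 0.86 (10% sensitivity off telemetry). With a 6/8 split they are 1.32 and 0.57 in the telemetry-only case.

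These figures rest on a constant background rate and an assumed placebo split. At up to 0.05 events per day the expected shift is under half a subject per active arm of 6 with a 6/6 split, and about half a subject in an IV arm with 6/8. It would therefore be too strong to say that 1000 mg IV will look safer than placebo; the expectation leans that way, but one chance event could outweigh it. The change is worth making because the study is not powered for testing and is read from small side-by-side percentages, where single events matter. The table shells are not among the documents, so whether they already carry a footnote on this cannot be checked.

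**What to change.** In SAP 9.5.1:

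1. Add a summary of cardiac and heart-rate treatment-emergent events with onset within 72 h postdose, for every arm against all placebo subjects. Select events by a prespecified list of MedDRA terms, not by how they were detected, since the documents do not say that detection method is recorded for each event. If only onset dates are available, use onset through Day 4; this leaves the part of Day 4 after IV telemetry ends unequal.
2. Show events from the same term list with later onset, up to 168 h, for SC doses against SC placebo only.
3. Keep the overall table, with a footnote giving telemetry duration by route.

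The cost is one or two tables, a term list and a footnote, with no change to study procedures. The drawback is that the later window has only about 6 to 8 SC placebo subjects, so it can be read only descriptively.
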